##### Muscle voluntary isometric strength

2.5.2.3

The maximum voluntary isometric strength of the lower limb muscles will be carried out using a load cell (Strength sensor kit, Chronojump Boscosystem^®^, Barcelona) connected to the corresponding software. This load cell has been previously validated and used in geriatric populations (Gaudet and Handrigan, 2020). Specifically, the gluteus medius, quadriceps, and hamstrings strength will be measured. Each measurement will be repeated 3 times (5 s contraction, 30 s rest), with a 2-minute rest between muscle assessments. The maximum and mean strength in the central 3 s of the contraction phase will be recorded from each repetition, then the average of the three repetitions will be used for the subsequent data analysis. To prevent accumulated fatigue from biasing the data, the sequence of muscle group assessments will be randomized across participants. Any repetitions showing a variation greater than 20% will be excluded, and an additional measurement will be subsequently obtained. On the other hand, upper limb strength will be assessed by determining handgrip strength with a hand dynamometer (Jamar™ Hidraulic Hand Dynamometer (Preston, Jackson, Missouri, EE.UU.). Three measurements of the dominant hand will be taken and the mean will be considered for further analysis. Higher values indicate greater muscle strength.

##### Quality of life EQ-5D-5L

2.5.2.4

Health-related quality of life will be evaluated using the EuroQol five-dimension, five-level questionnaire (EQ-5D-5L). This instrument consists of five domains reflecting key aspects of individual well-being and functional status: mobility, self-care, usual activities, pain/discomfort, and anxiety/depression. EQ-5D-5L index values will be derived using the Crosswalk Index Value Calculator provided by the EuroQol Group (Euroqol, 2023). Scores will range from -0.654 to 1, with values approaching 1 representing a more favorable health condition. The questionnaire has demonstrated excellent reliability, with ICC equal to or greater than 0.75 (Feng et al., 2021).

##### Lower limb muscle power

2.5.2.5

Lower limb muscle power will be evaluated using the Five Times Sit-to-Stand Test (5STST). This test quantifies the time required for an individual to stand up and sit down five consecutive times from a chair as quickly as possible, without using the upper limbs for support. This test has demonstrated excellent test–retest reliability in older adults, with ICC ranging from 0.89 to 0.99 (Bohannon, 2011).

##### Static and dynamic functionality and gait quality

2.5.2.6

Postural control and gait quality will be assessed using an inertial sensor integrated into the Android-based FallSkip^®^ system (Biomechanical Institute of Valencia, Spain) (Serra-Añó et al., 2020), following a previously validated protocol developed by our research group (Serra-Añó et al., 2019). The sensor will be positioned at the L4–L5 level, approximating the body’s center of mass. The assessment will consist of a continuous sequence including: (i) quiet standing for 30 s; (ii) walking as fast and as safely as possible over a 3-meter distance toward a chair at the sound of an acoustic signal; (iii) turning and sitting down; (iv) standing up; and (v) returning to the starting point at maximal safe speed. During the static standing phase, medial–lateral and anterior–posterior displacement, as well as the sway area of the center of mass, will be calculated in mm and mm^2^, respectively. Gait analysis will include vertical and medial–lateral range of the center of mass. Transitional movements (i.e., turning, sitting, and standing) will provide measures of: (i) standing-to-sitting time, (ii) standing- up power and (iii) sitting-to-standing time. Additionally, total task duration and reaction time to the auditory stimulus will be recorded.

##### Static and dynamic functionality and gait quality with a dual task

2.5.2.7

The procedure will replicate the previously described assessment protocol, with the addition of a dual-task condition (i.e., a concurrent cognitive task consisting of serial numerical subtraction from a random three-digit number while walking) (Liao et al., 2021; Zhou et al., 2014).

### Randomization (sequence generation, allocation concealment mechanism, implementation) and blinding

2.6

Participants will be assigned to the study groups (allocation ratio 1:1:1:1:1:1), through a computer-generated randomization sequence (SPSS statistical software, v29). This procedure will be conducted by an independent researcher who has no direct involvement in the trial, ensuring the neutrality of the allocation process. Group assignment will be concealed using sequentially numbered, opaque, sealed envelopes, which will be opened only after each participant is formally enrolled in the study. In addition, both the evaluator responsible for outcome assessments and the researcher who will perform the statistical analysis will be blinded to group allocation in order to minimize potential bias in data collection and interpretation.

### Sample size

2.7

Sample size has been calculated *a priori* using a type I error of 5% and a statistical power of 80% using the software GPower 3.1 (Universität Düsseldorf, Germany). Likewise, an effect size that would allow the minimum detectable change reported by Perera et al. (2006) was considered, based on the main variable ‘speed’ of 0.19 m/s, with a standard deviation of 0.29 m/s. Based on these premises, the number of participants required per group is 16. Assuming potential losses of 20%, the necessary sample size will be of 20 participants per group for a total sample of 80 participants.

### Data collection, management and confidentiality

2.8

Data collection will be conducted by trained physiotherapists assessors following standardized operating procedures to ensure consistency across the five assessment time points (T1–T5). All outcome measures, including functional tests, questionnaire data, and biochemical analyses, will be recorded using pre-specified case report forms and subsequently entered into a secure, password-protected electronic database hosted on institutional servers. To ensure confidentiality, each participant will be assigned a unique identification code to guarantee pseudonymization, and personal identifiers will be stored separately from research data. Data entry will be independently verified by a second researcher to minimize transcription errors, and automated range and consistency checks will be applied to detect implausible values. Access to the final dataset will be restricted to the principal investigator and the statistician, the former being blinded to group allocation. All study documents will be stored in locked cabinets in restricted-access facilities, and electronic data will be retained for the period required by institutional and regulatory policies. Data protection procedures will be reviewed and supervised by the Data Protection Officer, who oversees compliance with applicable data protection regulations. The University of Valencia is fully compliant with the General Data Protection Regulation (GDPR) and national data protection legislation. For any inquiries, suggestions, requests for the exercise of data subject rights, or amicable resolution of data protection-related issues, a dedicated contact address ([contact]) will be available, without prejudice to the right to lodge a complaint with the competent supervisory authority.

### Statistical analysis

2.9

Data analysis will be performed using the statistical program SPSS v29. For all studies, sample normality will be analysed using the Shapiro Wilk test, homoscedasticity using Levene’s test, and sphericity for the intra-subject factor using Mauchly’s test. For the comparison between groups, a mixed- design ANOVA will be used, with the between-subjects factor “group” (with the two groups included in each sub-study) and the intra-subject factor “time” including the five assessments. The dependent variables will be those described in the variable description section. The Bonferroni correction will be used for *post-hoc* comparisons. If there is a potential confounding factor that meets the requirements (independence and homogeneity of the lines) to be analysed as a covariate, ANCOVA will be used. The possible heterogeneity of the samples from each pair of groups (in each sub-study) in the baseline will be analysed using an independent samples One-way ANOVA. Differences will be considered statistically significant when the *p*-value is less than 0.05.

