##### Heart rate variability

2.5.2.2

Heart rate variability (HRV) will be continuously recorded using a chest strap device (Polar H10; Polar Electro Oy, Kempele; Finland) at three different time points: (i) 5 min at rest while lying in a supine position at the beginning of each assessment session; (ii) during the 6 mWT to evaluate the effect of the intervention in HRV in the exertional test at each of the time assessment points; (iii) during the first 20 min of the first session of each experimental intervention (i.e., VR/tDCS + walking) to explore acute effects of each intervention. Time-domain HRV indices will include mean RR interval duration (RRi), the standard deviation of normal-to-normal intervals (SDNN), the root mean square of successive differences between adjacent normal RR intervals (rMSSD), and the proportion of consecutive RR intervals differing by more than 50 ms (pNN50). Frequency-domain parameters will encompass low-frequency power (LF; 0.04–0.15 Hz), high-frequency power (HF; 0.15–0.40 Hz), the LF/HF ratio, and total power (TP). For statistical analysis, only the final segment of the recording will be considered, with the initial 2 min excluded to account for the stabilization phase (Pereira et al., 2016).

Data will be exported as.txt files from the Elite HRV application (Elite HRV LLC, USA) and subsequently analyzed using Kubios HRV version 3.5 (Kubios Oy, Finland). The recordings will be carefully reviewed to detect artifacts and ectopic beats (less than 3%), which will be manually corrected and substituted through interpolation based on adjacent RR intervals (Pereira et al., 2016).

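### One untransformed mixed ANOVA is fixed for every outcome and the normality test has no consequence; for LF/HF the verdict then depends on which band is the numerator, a minor and cheaply corrected weakness in secondary outcomes

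*Protocol article*

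**What the plan says.** Section 2.9 of the protocol article lists three checks: "sample normality will be analysed using the Shapiro Wilk test", Levene's test for equal variances and Mauchly's test for sphericity. It then prescribes a mixed-design ANOVA with group (two per sub-study) and time (five visits). On what is analysed, it says "The dependent variables will be those described in the variable description section". No transformation, alternative model or response to a failed check is given. The only switch named is to ANCOVA when a suitable confounder is found.

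Section 2.5.2.2 (Heart rate variability) lists eight indices. Among them are LF power, HF power, "the LF/HF ratio, and total power (TP"), with no logarithmic form. Plasma BDNF (2.5.2.1) is a concentration. In 2.5.2.6 the standing phase yields displacements "as well as the sway area of the center of mass", the latter in mm². All of these are secondary outcomes.

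The Sample size section (2.7) is based on walking speed and states that "the number of participants required per group is 16" before losses.

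**The concern.** Two things stand out. First, a test is announced that decides nothing. A reader cannot tell what the trialists will do when it rejects, and any response would be chosen after the data are seen.

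Second, the scale matters for some of these variables. LF/HF and HF/LF carry the same information, so a sound analysis should give the same verdict for both. A comparison of arithmetic means does not. LF, HF and total power are not quotients, but they cannot be negative. If their spread is large and treatment acts proportionally, a few large values dominate an untransformed mean and power falls. With 16 evaluable participants per arm there is little power to spare.

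**Working it through.** **Inputs from the protocol.** 16 evaluable per arm (2.7); two groups per comparison and five visits (2.9). The plan gives no figure for the outcomes at issue. Its effect and SD ("of 0.19 m/s, with a standard deviation of 0.29 m/s") concern walking speed, and nothing below rests on them.

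**Inputs assumed.** Lognormal data, log-SD 0.5 to 1.2, within-person correlation 0.6, and a true doubling in the active arm. For a lognormal variable CV = √(exp(σ²) − 1), so log-SD 0.5, 0.8, 1.0 and 1.2 correspond to CV 0.53, 0.95, 1.31 and 1.79.

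**Step 1: why the direction of a ratio matters.** If log(LF/HF) has mean μ and SD σ, the arithmetic mean of LF/HF is exp(μ + σ²/2) and that of HF/LF is exp(−μ + σ²/2). Their product is exp(σ²), which equals 1 only when σ = 0. At σ = 0.5 it is exp(0.25) = 1.28; at σ = 0.8 it is exp(0.64) = 1.90. The two means are therefore not reciprocals, and tests on them are different tests. On the log scale, log(HF/LF) = −log(LF/HF): the estimate changes sign and the p-value is identical. This needs no outside data; only its size depends on σ.

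**Step 2: size, simple comparison.** 20,000 simulated trials per row, two-sample t-test on the T1-to-T4 change. Repeat runs differ by a point or two.

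| Log-SD | Power untransformed | Power log | Loss (points) | LF/HF and HF/LF verdicts differ (untransformed) |
|---|---|---|---|---|
| 0.5 | 99% | 99% | 0 | 14% |
| 0.8 | 66% | 76% | 10 | 43% |
| 1.0 | 40% | 57% | 17 | 38% |
| 1.2 | 24% | 42% | 18 | 29% |

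With no true effect the untransformed test rejects in about 3–5% of trials and the log test in about 5%. The zero loss in the first row is partly a ceiling effect.

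**Step 3: size, planned model.** This used five visits, a group-by-time F test with Greenhouse-Geisser correction, 16 or 20 per arm and correlations 0.4–0.8. The effect was set for about 79% power on the log scale.

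- CV 0.31: untransformed power 76–80% for an upward effect; verdicts on the two directions differ in 17–18%.
- CV 0.53: 69–74%; differ in 29–31%.
- CV 0.95: 49–59%; differ in 43–44%.
- CV 1.31: 36–45%; differ in 40–42%.

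The pattern matches step 2. Away from the ceiling, a loss of 5–10 points already appears at CV 0.53. If the effect lowers the variable, 9–12 points are lost even at CV 0.31.

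**Step 4: the normality test.** Two groups by five visits give 10 cells per variable. A normal variable fails at least one with probability 1 − 0.95^10 = 0.401 if cells are independent, and in about 38% of trials when visits are correlated 0.6. A lognormal variable with log-SD 0.5 fails in about 42% of single samples of 16, and in about 98% of trials in at least one of the ten cells. The test will therefore often reject for normal and skewed variables alike, and the plan has no rule for either case.

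**Step 5: the reverse scenario.** Normal data with an additive effect of 0.8 SD, n = 16, correlation 0.6: untransformed power is 69%; log power is 63% at CV 0.20, 57% at CV 0.30 and 52–53% at CV 0.35. Logging then loses 6 to 17 points.

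**The case against.** The strongest reply is that this is largely an omission. The article nowhere says that values are analysed untransformed; that is the plain reading of a sentence. A statistical analysis plan that is not shown may hold a transformation rule. This limits the point but does not remove it: the section names one model for every described variable and a check without a consequence, so naming the scale improves what is written.

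A second reply is that section 2.5.2.2 fixes the direction as LF/HF, so nobody plans to test HF/LF. That stands. The disagreement rates measure how arbitrary the verdict is, not a choice the analysts have left themselves. They also concern one of eight listed HRV indices.

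Several stronger readings are tempting but unsupported:

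- *The plan loses power.* The protocol gives no SD, CV or skewness for any of these outcomes. Being positive does not make a variable lognormal; walking speed and strength are positive too.
- *All these outcomes share the ratio problem.* Only LF/HF is a quotient.
- *Shapiro-Wilk would let skewed variables pass.* That sets one test of a skewed variable against ten of a normal one. Over ten cells, moderate skew is nearly always flagged. The defect is the missing rule.
- *Logging is never worse.* It cannot lose in simulations built on lognormal data and multiplicative effects; step 5 shows that it can lose otherwise.
- *The trial's main or mechanistic conclusions are at risk.* The primary outcomes are frailty status and walking speed. HRV is absent from the stated specific objectives, and the Discussion's molecular argument rests on BDNF.

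**Conclusion.** The point holds in a limited form. Section 2.9 commits every described outcome to one ANOVA and announces a normality test that leads nowhere. For LF/HF, the dependence of the untransformed verdict on the direction of the ratio is a mathematical fact. Its size, about 14% of trials at log-SD 0.5 and 29–43% at 0.8–1.2, rests on an assumed lognormal model with a true doubling and 16 per arm.

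For LF, HF and total power, a loss of about 10–18 points at log-SD 0.8–1.2 is possible if effects are multiplicative. At 0.5 there is none under a doubling, although a smaller effect can show some. For BDNF and sway area the documents support only a request to fix the scale in advance. The primary outcomes and the sample size calculation are untouched. This is a minor improvement that is worth making because it is cheap.

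**What to change.** In section 2.9, or in the statistical analysis plan before any unblinded data are seen:

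- Analyse LF, HF, total power and LF/HF on the natural-log scale, and report active/sham ratios of geometric means with 95% confidence intervals.
- For plasma BDNF and sway area, name the scale in advance: log if a multiplicative effect is expected, otherwise untransformed.
- Do not let a cell-by-cell Shapiro-Wilk test choose the scale. Check model residuals instead, and say what will follow if they are clearly unsatisfactory.
- Leave walking speed, strength and the remaining outcomes as they are.

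The change is to wording only; data collection and sample size are unaffected. The costs are that results for the logged variables are expressed as ratios, and that power falls by about 6–17 points at CV 0.20–0.35 for any variable that is in fact normal with an additive effect.

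### The five-visit ANOVA needs complete rows and leaves covariate adjustment conditional; a baseline-adjusted mixed model keeps more participants and fixes the covariate in advance

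*Protocol article*

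**What the plan says.** All of the following is in the protocol article.

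- **Section 2.9, main analysis.** "For the comparison between groups, a mixed- design ANOVA will be used". The between-subjects factor is group ("with the two groups included in each sub-study"), and the within-subjects factor is described as "intra-subject factor “time” including the five assessments". The software is SPSS v29. Sphericity is to be checked with Mauchly's test, which identifies this as a classical repeated-measures ANOVA. Post-hoc comparisons are Bonferroni-corrected.
- **Section 2.9, covariates.** ANCOVA is conditional: "If there is a potential confounding factor that meets the requirements", namely independence and homogeneity of the regression lines. No covariate is named.
- **Section 2.9, baseline.** In a separate, later sentence, heterogeneity between the groups "in the baseline will be analysed using an independent samples One-way ANOVA".
- **Section 2.7.** The sample size rests on walking speed: a difference of 0.19 m/s, SD 0.29 m/s, 16 per group, then "Assuming potential losses of 20" per cent, giving 20 per group and 80 in all.
- **Section 2.1.** The visits are T1 (baseline), T2 (after the first session), T3 (4 weeks), T4 (end of the 8 weeks) and T5 (4-week follow-up). No primary time point is named.

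**The concern.** Three features of the stated method work against the trial.

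1. **Complete rows.** A classical repeated-measures ANOVA needs a value at every level of time. Without imputation, a participant seen at T1 to T4 but absent at T5 contributes nothing, not even to the T4 comparison. If drop-out is related to earlier performance, the completers are also a selected group.
2. **Undefined adjustment.** Homogeneity of slopes can be checked only once outcome data are available, and the candidate covariate is left open. Whether to adjust, and for what, is therefore settled after the data are seen. Testing baseline differences for significance does not help: under proper randomisation any such difference is due to chance.
3. **Loose target.** The omnibus group-by-time test gives no estimate at any visit. A post-hoc comparison of two groups at one visit compares raw means and ignores baseline walking speed.

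At stake are precision in comparisons of about 40 people each, and protection against choosing the adjusted or unadjusted result afterwards.

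**Working it through.** **Plan's own figures.** The loss step reproduces: 16 / (1 − 0.20) = 20 per group, and 4 × 20 = 80. The standardised difference is 0.19 / 0.29 = 0.655. For an unadjusted two-sided comparison of two groups at 80% power this needs 38 per group, so the 16 does not follow from those inputs. That is a separate matter, but it means that the trial has little precision to spare.

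**Assumptions.** The article gives no correlation between visits and no missingness rate beyond 20% losses. The correlations r = 0.5, 0.7 and 0.8 and the visit-level rates below are assumed.

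**Complete rows.**
- At 5% independent missingness per post-baseline visit, 1 − 0.95⁴ = 18.5% lack at least one visit, while 5% lack T4. Completers per group: 20 × 0.815 = 16.3.
- With 20% drop-out starting equally often at T3, T4 or T5, plus 3% of follow-up visits missed at random, complete rows number 40 × 0.80 × 0.97⁴ = 28.3 of 40. Those with T4 number 40 × (1 − 0.20 × 2/3) × 0.97 = 33.6 of 40. The sample size counts on 32.

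**Baseline adjustment at T4, 16 per arm, two-sided 5%.** Noncentrality = 0.19 / (0.29 × √(1 − r²) × √(2/16)).

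| Analysis | Noncentrality | Power |
|---|---|---|
| Unadjusted | 1.853 | 43% |
| r = 0.5 | 1.853 / 0.866 = 2.140 | 54% |
| r = 0.7 | 1.853 / 0.714 = 2.595 | 71% |
| r = 0.8 | 1.853 / 0.600 = 3.088 | 85% |

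**Against the planned group-by-time test.** Simulation with 20 per arm randomised and equal correlation r between all visits. Effects at T1 to T4 are 0, 0, 0.095 and 0.19 m/s; at T5 the effect is 0.19 (held) or 0.095 (half faded). Power in % for r = 0.5 / 0.7 / 0.8:

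| Scenario | ANOVA group-by-time, completers | T4 ANCOVA, all with T4 |
|---|---|---|
| Held, no missing data† | 60 / 85 / 97 | 63 / 82 / 91 |
| Held, 20% drop-out | 51 / 74 / 91 | 55 / 73 / 86 |
| Held, 20% drop-out + 3% missed† | 42 / 67 / 85 | 55 / 72 / 85 |
| Faded, no missing data† | 43 / 68 / 87 | 63 / 81 / 91 |
| Faded, 20% drop-out | 37 / 57 / 78 | 57 / 73 / 87 |
| Faded, 20% drop-out + 3% missed | 32 / 52 / 71 | 55 / 71 / 85 |

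† ANOVA with Greenhouse-Geisser correction. In the last row that correction would give 30 / 47 / 69, so gaps of 2 to 5 points between marked and unmarked rows mean little.

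A baseline-adjusted mixed model with drop-out and missed visits gave about 60 / 74 / 88 (held) and 56 / 73 / 87 (faded, 600 runs), with type I error of 0.04 to 0.055.

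**The case against.** The best defence has five parts.

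- **Deletion is not a stated rule.** A reader might infer that the article orders incomplete cases to be dropped. It does not; this is a property of the method, and imputation could be specified in an analysis plan that is not shown. This stands, and the point is worded accordingly.
- **Baseline testing is not tied to ANCOVA.** A reader might infer that a significant baseline test triggers adjustment. The two sentences are separate and nothing links them. This stands. What remains is that adjustment is conditional and its covariate unnamed.
- **Baseline is not ignored altogether.** T1 is a level of time, so the interaction already reflects change from baseline. This stands for the omnibus test. It does not cover a post-hoc group comparison at one visit.
- **Losses may fit the allowance.** The 18.5% is below the planned 20%, and missing only T2, held right after the first session, is unlikely; with three visits at risk the figure is 1 − 0.95³ = 14.3%. This is fair. The allowance is exceeded only if missed visits come on top of 20% drop-out.
- **A T4 contrast is a choice.** Section 2.1 justifies every visit and ranks none. This stands: T4 is a proposal, not the article's own target.

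**Conclusion.** The point holds as an improvement worth making, not as an error that invalidates the trial. The named method is wasteful when visits are missed, and the covariate rule leaves adjustment open until outcome data are seen.

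The size depends on assumptions. It is tempting to read the rise from 43% to between 54% and 85% as the gain over the plan, but the 43% belongs to a raw T4 comparison, which is not the planned omnibus test. Against that test the gain is clear when the effect fades by T5, or when visits are missed and correlation is moderate: 23, 19 and 14 points in the last row of the table (55 − 32, 71 − 52, 85 − 71). With a held effect and only drop-out, it is 4 points at r = 0.5, about nil at 0.7 and −5 at 0.8. Nor should low power of the group main effect be held against the plan, since the article does not name that effect as the deciding test.

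The claim that the alternative costs nothing would also go too far. It assumes data missing at random, and an unstructured covariance over T2 to T5 has 4 × 5 / 2 = 10 parameters, estimated from about 40 people per comparison.

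**What to change.** Amend section 2.9 before any unblinded analysis.

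1. For continuous outcomes, including walking speed, replace the ANOVA with a linear mixed model (SPSS MIXED) using all randomised participants with any post-baseline value. Responses are T2 to T5; terms are baseline value, group, visit and group-by-visit. State unstructured covariance, a simpler fallback if the model does not converge, and small-sample degrees of freedom.
2. Name one time point in advance and report active minus sham there with a 95% confidence interval. The end of treatment, T4, is the natural choice. A T4 ANCOVA on everyone seen at T4 is a simpler, nearly equivalent option.
3. Always include the baseline value. Delete the conditional ANCOVA rule and the baseline significance tests; describe baseline by group instead.

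Frailty status, the other primary outcome, is categorical. It needs its own model and is not covered here.

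**Cost.** A change of wording and slightly more modelling work, with the same data and software and no extra participants or visits. The price is the missing-at-random assumption, the covariance choice, and some loss of power against the omnibus test if data are nearly complete, correlation is high and the effect persists.
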